## Abstract

**Background:**

As primary care populations age, timely identification of palliative care need is becoming increasingly relevant. Previous studies have targeted particular patient populations with life-limiting disease, but few have focused on patients in a primary care setting. Toward this end, we propose a stepped-wedge pragmatic randomized trial whereby a machine learning algorithm identifies patients empaneled to primary care units at Mayo Clinic (Rochester, Minnesota, United States) with high likelihood of palliative care need.

**Methods:**

42 care team units in 9 clusters were randomized to 7 wedges, each lasting 42 days. For care teams in treatment wedges, palliative care specialists review identified patients, making recommendations to primary care providers when appropriate. Care teams in control wedges receive palliative care under the standard of care.

**Discussion:**

This pragmatic trial therefore integrates machine learning into clinical decision making, instead of simply reporting theoretical predictive performance. Such integration has the possibility to decrease time to palliative care, improving patient quality of life and symptom burden.

**Trial registration:**

Clinicaltrials.gov NCT04604457, restrospectively registered 10/26/2020.

**Protocol:**

v0.5, dated 9/23/2020

## Background

Palliative care aims to improve quality of life, decrease symptom burden, and guide value-concordant care for patients dealing with serious illness. Early integration of palliative care has been shown to improve quality of life (QOL) and mood for patients and decrease health care resource utilization [1–5]. Involvement of palliative care is increasingly important at a population level with the increasing age and medical complexity of populations. Therefore, timely identification of palliative care need is critical. Such identification of patients with a need for palliative care can be difficult, however, at a primary care population level. The use of artificial intelligence has been postulated as a way to help with timely identification of patients [6].

However, integration of machine learning algorithms into clinical practice proves to be more difficult than simply reporting theoretical performance. Previous studies suggest that even among patients predicted by an algorithm to have high palliative care need, providers may believe that palliative care needs are negligible or already being met [7]. Other studies suggest that engagement of primary care providers, patients, and caregivers might be difficult, in some cases because palliative care is misunderstood or negatively perceived [8–10]. Therefore, performance of an algorithm is likely to be lower in practice than it would be in a hold-out set in model development. Pragmatic trials are a meaningful mechanism to examine the real-world impact of algorithms on clinical decision-making. Courtright et al applies the pragmatic trial framework in the context of palliative care, but offers insight only into the inpatient population [7]. There is need, therefore, for an outpatient-focused pragmatic clinical trial to examine the effect of machine learning on referral to palliative care.

The primary aim of this study is to assess the impact of the integration of a machine learning algorithm into clinical workflow within a primary care population. Our hypothesis is that the integration of the algorithm will reduce the time to palliative care consultation for patients in the primary care outpatient setting.

## Methods/Design

### Setting

Mayo Clinic (Rochester, MN, United States) is an academic medical center with a community primary care population of approximately 119,000 adult patients, consisting of 42 care teams nested within 9 care team clusters across 5 different sites.

### Algorithm development

Adult patients assigned to a primary care unit from October 1, 2018, to December 31, 2019, were included; patients under 18 were excluded. Hospice and death were considered censoring events, and patients were removed from the data for 75 days following a palliative care consult. Historical data from the primary care population were obtained, yielding 116108 unique patients and 571 palliative care consults. A time-to-event Poisson gradient-boosting machine (GBM) with time-dependent covariates was trained to predict presence of a palliative care consult. To reduce the overall training time, model selection and training were done on a subset of the training data, with a 10-1 control-case ratio. Nested cross-validation was used to optimize tuning parameters. Covariates included age, sex, lab values, diagnosis codes, clinical note metadata, opioid usage, pain scores, prior inpatient utilization, and time since last appointment. The mean training survival concordance (c-statistic) obtained in cross-validation was 0.96.

**Fig. 1 Fig1:**
[figure not shown]
A custom user interface to present the top 40 patients as predicted by the algorithm

Weekly, the palliative care specialists will review the presented patients and make determinations on the appropriateness of palliative care referral, performing chart review if necessary to find patient characteristics that may aid decision-making. The palliative care specialist will then have the option to “snooze” a patient (reject them for 90 days), “short snooze” (review again in 2 weeks) or “accept” a patient (determine that palliative care referral is recommended for the patient). For accepted patients in the treatment arm, the palliative care specialist will reach out to the patient’s Primary Care Provider (PCP) via message in the electronic record to request that they consider a palliative care consult for the patient and order consultation if deemed appropriate. Therefore, the algorithm makes no clinical decisions; rather, the palliative care specialists leverage the algorithm for recommendations, and specialists and PCP together determine if palliative care is appropriate for each patient. Accepted patients in the control arm are not acted upon, but may continue to receive palliative care under the standard of care. Because of this, the trial has no blinding: palliative care and primary care specialists are informed which units are on which arms at what times.

Care team clusters were randomized (computer generated) into a seven-cluster stepped-wedge design matrix (Fig. 2). Several clusters were grouped together based on distribution of predicted palliative care score in historical data. New care teams will enter the treatment arm every 42 days. In this way, the first wedge sees all units on the control arm, and the last wedge sees all units on the treatment arm.

**Fig. 2 Fig2:**
[figure not shown]
The stepped-wedge design matrix. Nine care teams were randomized into 7 wedges

### Outcomes

The primary outcome is timely identification of palliative care consultation. This is measured as time to record of consult in the electronic health record by the palliative care team in the outpatient setting. Since the primary hypothesis was to reduce the time to palliative consult (in part by reducing the time to identification of palliative need), a time-to-event primary outcome was chosen over an outcome involving presence/absence of palliative consult. The secondary outcomes are: Number of palliative care consultations over the study duration in each armNumber of advanced care planning notes documented in the electronic health record in each armNumber of billing codes (ICD-10) for palliative care in each armPositive predictive value (PPV) of screened patients: the percentage of patients presented for review who (1) are accepted by the palliative care specialists or, separately, (2) are accepted by both palliative care specialists and primary carePerformance metrics on palliative care specialist/PCP handoff: descriptive statistics on time between PCP contact and PCP responseSummarized patient data will be characterized by age, sex, and model probability as well as important static and time-varying covariates used in the algorithm. All patients will be analyzed on an intention-to-treat status regardless of whether they were accepted or not and will be extended to the cluster status in the event of care team change between intervention and control units.

### Analysis

For all study outcomes Bayesian hierarchical modeling will be used to adjust for the key features inherent in the stepped-wedge design. Particularly, time-to-event modeling will be used to model timely palliative care, the main study outcome, and other time-to-event or count outcomes. The time of event will consist of a heterogeneous Poisson process, allowing for adjustment to the event rate due to secular time effects and unit clustering through random effects. Unit clustering will be treated with normal random effects and the secular trend will be modeled with time series autoregressive prior of order 1. Statistical tests will be based on 95% credible intervals. For secondary binary outcomes, logistic regression will be used with the same design features.

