### Power

To take account of the complex nature of the design, power was estimated using Monte Carlo simulation [11]. The model for the simulation consisted of a hierarchical Poisson regression with the outcome being time to palliative care. Random effects for cluster as well as a time series autoregressive model for secular trend were integrated to correctly specify the wedge design. To estimate reasonable parameters for this model pilot data were collected for all patients paneled to Mayo Clinic Primary Care teams as of September 2018 (n=154,312). For each patient, their palliative care consult status from the medical record and estimated probability from the algorithm were collected. With estimates of the intra-correlation of clusters (i.e., the rate of palliative care per care team), and secular trend estimated from data we have at least 80% power with reasonable PPVs in several scenarios for the trial timeframe to detect Incident Rate Ratios of 2.0 or greater with the stepped wedge design. See Fig. 3 for the power curves; various scenarios with varying number of clusters and time windows were tested.

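### The Poisson model named for the note and billing-code counts has no term for repeat records from one patient, so its 95% credible intervals are too narrow if those records bunch within a wedge

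*Protocol article*

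**What the plan says.** The Outcomes section of the Protocol article lists, among the secondary outcomes, the number of advance care planning notes and the number of palliative ICD-10 billing codes in each arm. Both are totals of records. Neither is defined as patients with a record or as first records.

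The Analysis section assigns them a model: "time-to-event modeling will be used to model timely palliative care, the main study outcome, and other time-to-event or count outcomes". It describes that model in these words: "The time of event will consist of a heterogeneous Poisson process, allowing for adjustment to the event rate due to secular time effects and unit" (meaning care-team clustering). It then gives the form of both terms: "Unit clustering will be treated with normal random effects and the secular trend will be modeled with time series autoregressive prior of order 1". The decision rule is "Statistical tests will be based on 95% credible intervals".

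The Abstract gives the layout: "42 care team units in 9 clusters were randomized to 7 wedges, each lasting 42 days". A unit is therefore a care team. The section names no patient-level effect, dispersion parameter or rule for repeat records.

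**The concern.** Conditional on its rate, a Poisson process has variance equal to its mean and independent events. That is reasonable for a time to consult. It is doubtful for notes and codes, because one palliative episode can generate several records in the same patient within days or weeks. Such bursts differ by team and by period. A constant team effect cannot absorb them, and neither can a time trend shared by all teams.

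The model then sees more independent information than exists. A few heavily documented patients who happen to fall in one arm could push a 95% credible interval clear of no effect when the intervention has changed nothing. At stake is how two secondary outcomes are read.

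**Working it through.** **The plan's own figures.** The article states no type I error, dispersion or power for these two counts, so there is nothing to reproduce for them. Its one power statement concerns the primary outcome: at least 80% power "to detect Incident Rate Ratios of 2.0 or greater with the stepped wedge design". The simulation parameters are not given, so only a rough bound is possible.
- The Schoenfeld formula needs 66 events for a ratio of 2.0.
- Algorithm development reports a historical extract "yielding 116108 unique patients and 571 palliative care consults" over October 2018 to December 2019, which is 457 days.
- Scaled to 7 × 42 = 294 days, this is 571 × 294/457 ≈ 367 consults.
- Power before any loss to clustering exceeds 0.99, so the power statement is not contradicted.

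**Inputs.** From the article: 42 teams, 7 periods of 42 days, Poisson counts with unit and time effects, and a 95% interval taken as a 5% two-sided test. Assumed, because the article is silent: a geometric number of records m per episode with mean μ from 1 to 3, the lag of later records, and between-team variation (log-rate SD 0.3).

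**Formula.** If all m records of an episode fall in the same team and period, the count has D = E[m²]/E[m] times the Poisson variance. For a geometric count, E[m²] = 2μ² − μ, so D = 2μ − 1. The false-positive rate is then α = 2(1 − Φ(1.96/√D)). For example, μ = 1.5 gives D = 2, 1.96/√2 = 1.386 and α = 16.6%.

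**Check by simulation under no effect.** The analysis was Poisson regression with team and period effects, standing in for the Bayesian model. The design matrix figure is not shown, so 7 and 8 periods were both run, with 1,500 trials per setting. The μ = 3 row comes from separate runs of 300 and 500 trials.

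| μ | D | Formula | Simulated, repeats in same wedge (7 / 8 periods) |
|---|---|---|---|
| 1 | 1 | 5.0% | 4.1% / 5.1% |
| 1.25 | 1.5 | 11.0% | 11.0% / 9.7% |
| 1.5 | 2 | 16.6% | 15.6% / 16.5% |
| 2 | 3 | 25.8% | 24.3% / 25.3% |
| 2.5 | 4 | 32.7% | 32.6% / 29.7% |
| 3 | 5 | 38.1% | 35% to 38% |

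The μ = 1 row is close to nominal, so the excess comes from the repeats. From μ = 1.25 to 3 the range is about 10% to 38%, or 10/5 = 2 to 38/5 = 7.6 times nominal.

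**Timing.** With μ = 2 and later records at exponential lags, 1,000 trials per setting gave:
- mean lag half a wedge: 19% to 20%
- one wedge: 14% to 18%
- three wedges: 7%

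Across μ = 1.25 to 3, a mean lag of one wedge gave about 6% to 24%, and three wedges about 5% to 9%. A stable patient-level rate over the whole study gave 5.3% to 5.5%, because the team effect absorbs it.

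**Remedies under the same null.** A Pearson-type dispersion scale gave 4% to 7%, a negative binomial 5% to 11%, and counting each episode once 3% to 6%. A unit-by-period random effect was not simulated.

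**The case against.** The strongest objection is that this is a one-paragraph analysis section in a condensed article. It names two variance terms but does not say they are the only ones. A fuller plan could add a dispersion term or a rule for duplicate records. That much stands: a reader might infer that the plan excludes any such term, and the text does not support that. However, the article is not merely silent. It names the distribution, the sources of heterogeneity and the prior form of each, and extends that model to count outcomes. Followed as written, it fits these two outcomes badly.

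The second objection is that the size has no input from the documents. This also stands. A reader might take a fixed multiple, such as three to six times nominal, as the trial's error rate. By the formula, that band needs D between about 1.85 and 3.58, with repeats in the same wedge. The article gives neither dispersion nor timing, and with repeats spread out the error is near nominal.

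The low end is also uncertain. One small run (250 trials) gave 7% at μ = 1.25 in the same wedge, against 10% to 11% in the larger runs. The standard error at 11% is √(0.11 × 0.89/250) ≈ 2 points, so the gap is about two standard errors.

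Finally, all the simulations used a frequentist fixed-effects model, not the Bayesian model with its autoregressive prior. They show the mechanism and approximate size, not the exact operating characteristics.

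**Conclusion.** The point holds in conditional form. The model named for the note and code counts treats repeat records from one patient as independent, and its intervals are too narrow when those records bunch in time. Under the assumed geometric counts (mean 1.25 to 3 records per episode), the inflation runs from twice to more than seven times nominal with repeats in the same wedge. It falls to almost none when repeats spread over several wedges or reflect a stable patient rate. Where this trial lies in that range cannot be determined from the article.

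A reader might extend the point to the main result. The documents do not support that: the primary outcome is a time to consult, and neither it nor its power statement depends on how repeat notes and codes are handled. The point is a cheap improvement of minor priority.

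**What to change.** For these two outcomes, keep the unit and secular-trend terms and add one term for extra-Poisson variation: a unit-by-period random effect, a negative binomial or a dispersion scale. Alternatively, analyse the number of patients with at least one note or code per wedge and report total records descriptively. The article should also state how repeat records are counted.

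The cost is a sentence in the Analysis section and, for the first option, one more parameter in the model. No new data are needed. The downside is somewhat wider intervals for two secondary outcomes. If repeats prove rare, the extra term changes little. Of the modelling options, the dispersion scale came closest to 5% in the checks and the negative binomial removed most of the inflation. The unit-by-period effect should be checked by simulation before it is adopted.

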### Power

To take account of the complex nature of the design, power was estimated using Monte Carlo simulation [11]. The model for the simulation consisted of a hierarchical Poisson regression with the outcome being time to palliative care. Random effects for cluster as well as a time series autoregressive model for secular trend were integrated to correctly specify the wedge design. To estimate reasonable parameters for this model pilot data were collected for all patients paneled to Mayo Clinic Primary Care teams as of September 2018 (n=154,312). For each patient, their palliative care consult status from the medical record and estimated probability from the algorithm were collected. With estimates of the intra-correlation of clusters (i.e., the rate of palliative care per care team), and secular trend estimated from data we have at least 80% power with reasonable PPVs in several scenarios for the trial timeframe to detect Incident Rate Ratios of 2.0 or greater with the stepped wedge design. See Fig. 3 for the power curves; various scenarios with varying number of clusters and time windows were tested.

**Fig. 3 Fig3:**
[figure not shown]
Power curves estimated using Monte Carlo simulation

### Approvals

All study activities were approved by the Mayo Clinic Institutional Review Board (ID 20-005977). Waivers of consent were granted for both patients and providers. Updates to the protocol are always communicated to the study team by email, and to participating care teams by a variety of electronic and in-person formats. Results of the study will be published as appropriate.

### Monitoring

Because there are minimal risks to this study, no formal monitoring committee was formed, nor will interim analyses be performed.

### Security/Privacy

All clinical data is pulled directly from the electronic health record, and is maintained on password-protected servers. Additionally, these data are stored in a secure MariaDB SQL database that the user interface accesses; both the user interface and the SQL database are password-protected and available only to palliative care specialists and statistical personnel.

## Discussion

Herein is described a pragmatic clinical trial to discern the effect of a machine learning algorithm on the timeliness of receipt of palliative care for patients in an outpatient primary care setting. Previous studies [7] have examined this relationship in the inpatient setting, but additional challenges are present in the outpatient setting. In particular, primary care providers may be difficult to engage, as they may have misperceptions about palliative care and less of a relationship with the palliative care specialty than inpatient physicians do.

Nevertheless, this trial retains the strengths of a pragmatic trial. Waivers of consent were obtained for both patients and providers, lessening the burden on patients and the clinical practice. This will make for easier integration of the algorithm into the practice. In addition, palliative care specialists will be reviewing the algorithm’s recommendations, lessening the number of false positives that reach the primary care physicians and hence any alarm fatigue. The specialists will also reach out to the primary care physicians directly, so referrals will come from a colleague instead of simply from an unfamiliar algorithm. Finally, the study endpoints are all available electronically as part of the electronic health record or the custom user interface.

One limitation of the pragmatic setup of this trial is the possibility of historical palliative consults being skewed toward certain populations or under-labeled in certain populations. Nevertheless, any subgroup of the patient population in which the algorithm experiences deficiencies will still experience palliative consults under the standard of care. For any subgroup toward which the label is skewed or more highly labeled, those patients will have their palliative needs met more effectively after being identified by the algorithm. Therefore, this study is still valuable to identify unmet palliative needs and because of its pragmatic nature can be easily implemented.

## Data Availability

Not applicable.

## Abbreviations

GBM: Gradient Boosting Machine
PCP: Primary Care Provider
PPV: Positive Predictive Value
QOL: Quality of Life
